## **8.5. Study participants**

The study participants are TB patients and their healthcare providers, while the primary participants are TB patients. Objectives of the study related to medication adherence and treatment outcomes will rely solely on data collected from patients, while objectives related to usability, cost-effectiveness, acceptability, and behavioral and socio-cultural factors will rely on data collected from both patients and providers.

### **8.5.1. Study participants (TB patients)**

#### **8.5.1.1. Study population**

The efficacy studies target TB patients. The source population will be all new patients with TB symptoms who come to a study site and undergo bacteriological screening during the study period or TB patients bacteriologically confirmed elsewhere and referred to a study site for TB treatment.

#### **8.5.1.2. Inclusion criteria**

Inclusion criteria will include:

- Patients with new, or previously treated, bacteriologically-confirmed drug-sensitive pulmonary TB
- Eligible to start the standard 6-month first-line anti-TB medication
- Outpatient status at the time of screening and enrollment
- Men or women age  $\geq 18$  years
- Able and willing to provide informed consent

#### **8.5.1.3. Exclusion criteria**

The exclusion criteria will include:

- Patients with known DR-TB
- Any condition that causes cognitive impairment such as severe acute illness or injury, developmental retardation, or severe psychiatric illness and thus precludes informed consent or safely participating in the study procedures

- Inpatient status at the time of screening and enrollment
- Expected to move away from the study site or become incarcerated before the final study follow up at month two
- Concurrent extra-pulmonary TB
- Contraindicated medications
- Active liver disease that requires a TB regimen other than HREZ - isoniazid, rifampicin, pyrazinamide, and ethambutol.

#### **8.5.1.4. Justification for inclusion and exclusion**

DR-TB patients take TB medications over a long time and as an inpatient, thus are unable to experience SAT. Similarly, inpatients, as they are admitted and assigned a bed to receive treatment and care, are unable to effectively experience the SAT.

#### **8.5.1.5. Sampling and sample size**

The sample size is calculated considering a 1-sided type I error of 2.5%, a power of 80%, 10% attrition rate, delta of 20%, non-inferiority margin, and a continuous outcome of percentage adherence over the two-month intensive phase, with a standard deviation of 36% and 79% of average adherence, assuming null hypothesis for both arms. The results yield a sample size of 57 in each arm for a total of 114 participants. We will do a  $\log_{10}$  transformation on the data, where a difference can be equivalently transformed into a ratio using a power ( $10^3$ ). The non-inferiority will be calculated as the log in the control minus the log in the intervention, which is equivalent to the log of the control divided by intervention.

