## **9. STATISTICAL ANALYSIS**

Descriptive summary measures will be used to report participant characteristics. Chi-square tests will be used to evaluate potential associations among categorical variables. To compare the level of adherence between study arms and among variables, independent t-tests will be done on log-

transformed adherence percentage of the expected 60 days. Effects of the arms and other adherence variables will be estimated using a geometric mean (GM) with geometric standard deviation (GSD) and mean ratios (MR) with 95% confidence intervals (CI). Log binomial regression will be conducted to identify risk factors of at least one negative isoniazid urine test and self-reported adherence of participants. Effects will be measured using adjusted relative risk (ARR) with 95%CI. A general linear model will be done on log-transformed adherence percentage to identify the effects of variables on participants' level of adherence. Effects will be measured using an adjusted mean ratio (AMR) with 95% CI.

Descriptive statistics including frequency and percentage will be used to describe the health state of the study participants. Multiple bar charts with cross-tabulation will be used to illustrate distributions of health states by study arms. Chi-square and Fisher's exact tests will be employed to compare the five EQ-5D-5L health domains by study arms. Kolmogorov–Smirnov, Shapiro–Wilk tests, and median values with interquartile range (IQR) will be used to summarize EQ-5D-5L index value/utility. Nonparametric Mann–Whitney U test will be employed to compare the difference in EQ-5D-5L index value/utility among study arms. A log-binomial model will be used to identify risk factors for lower HRQoL, which is having at least one health problem.

The overall TB treatment cost will be estimated by considering costs related to anti-TB drug pick-up, guardian costs, and coping costs over the two-month intensive phase. The proportion of study participants who faced catastrophic costs at a cut-off point of 20% will be estimated. A cross-tabulation will be employed to evaluate the distribution of catastrophic cost over the study arms and chi-square test will be used to test the association between catastrophic cost and study arms.

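### The margin, SD and 57 per arm are set on raw percentage adherence, but non-inferiority is judged on a log ratio with no stated margin, so the decision rule is undefined and the 80% power is unsupported

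*Protocol*

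**What the plan says.** Protocol section 8.5.1.5 takes a one-sided type I error of 2.5%, 80% power, a "10% attrition rate" and a "delta of 20%, non-inferiority margin". The calculation is for "a continuous outcome of percentage adherence over the two-month intensive phase, with a standard deviation of 36% and 79% of average adherence", with both arms given the same mean ("assuming null hypothesis for both arms"). The result is 57 per arm, 114 in total.

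The same paragraph then announces a log10 transform and fixes the comparison: "The non-inferiority will be calculated as the log in the control minus the log in the intervention", which it equates with the log of a control-to-intervention ratio.

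Section 9 confirms that scale. The arms are compared by independent t-tests on log-"transformed adherence percentage of the expected 60 days", and effects are reported as geometric means and mean ratios with 95% confidence intervals. Section 9 mentions no margin.

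**The concern.** A non-inferiority conclusion rests on comparing a confidence limit with a margin, and both must be on the same scale. Here the margin is a difference in percentage points and the confidence limit is for a ratio. One cannot be turned into the other without a choice that the protocol does not make.

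Two things are at stake. First, the conclusion could turn on a conversion chosen after the data are seen. For example, an upper limit of 1.28 for the control-to-intervention ratio passes a margin of 1.34 and fails 1.25 and 1.20. Second, the power calculation describes a test that the protocol does not plan to run.

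The transform also suits this outcome poorly. Adherence out of 60 days is capped at 100%, so its tail lies on the low side, and a log stretches that tail.

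**Working it through.** **1. Reproduce the stated sample size.** Inputs from section 8.5.1.5: SD 36, margin 20, true difference 0, one-sided alpha 0.025 (z = 1.960), power 0.80 (z = 0.842), attrition 10%.

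n = 2 × (1.960 + 0.842)² × 36² / 20² = 50.9, so 51 evaluable per arm. 51 / 0.9 = 56.7, so 57 per arm. This matches, and normal-approximation power at 51 per arm is 80.1%.

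If 20% is read as relative to the mean (0.20 × 79 = 15.8 points), n is 82, or 92 after attrition, which does not match. The margin used was therefore 20 raw points.

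**2. What 20% could mean as a ratio.**
- Converted at the assumed mean: 79 / (79 − 20) = 79/59 = 1.34, ln 0.292
- Intervention at least 80% of control: 1/0.80 = 1.25, ln 0.223
- Control at most 120% of intervention: 1.20, ln 0.182

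**3. The log SD that would give 80% power at 51 per arm.** SD(ln) = ln(margin) / [2.80 × √(2/51)], which is 0.526, 0.402 and 0.329 for the three margins. The protocol gives no log-scale SD to set against these.

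**4. Log-scale power if adherence were log-normal (assumption).** CV = 36/79 = 0.456; SD(ln) = √ln(1 + 0.456²) = 0.434. Power = Φ[ln(margin) / (0.434 × √(2/51)) − 1.960].

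**5. Log-scale power if adherence is bounded and left-skewed (assumption).** Beta distribution with mean 0.79 and SD 0.36 (parameters 0.221 and 0.059), then binomial over 60 days; 51 per arm, identical arms, 20,000 replicates. About 8% of simulated participants have zero days, and values below the floor are set to the floor. SD(ln) is about 1.30 with a floor of 1/60. The raw-difference test in the same model has about 79% power.

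| Scenario | Margin 1.34 | 1.25 | 1.20 |
|---|---|---|---|
| Log-normal | 92% | 74% | 56% |
| Bounded, floor 0.5/60 | 17% | 12% | about 10% |
| Bounded, floor 1/60 | 21% | 14% | 10% |
| Bounded, floor 10% adherence | 44% | 28% | 20% |

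Raising the lowest values to 10 or 15 of 60 days gives 60% and 78% at margin 1.34, although a floor that high also pulls the raw SD below 36.

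**6. Which scenario fits the protocol's own figures better.** On a 0–100% scale with mean 79%, the SD cannot exceed √(79 × 21) = 40.7. The assumed 36 is 36/40.7 = 88% of that, which implies many participants near 100% and a group near zero. The log-normal in step 4 has median 79/√(1 + 0.456²) = 71.9, so it puts 1 − Φ[ln(100/71.9)/0.434], about 22%, of participants above 100%, which is impossible.

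**7. How the log weights low values.** With everyone else at 100%, four of 51 participants at 1/60 days give an arithmetic mean of (47 + 4/60)/51 = 92.3% and a geometric mean of (1/60)^(4/51) = 72.5%.

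**The case against.** A reader might infer that the planned test is known to fall short of 80% power, or that the trial would probably fail even with identical arms. The protocol does not support either statement. Log-normal data with margin 1.34 give 92%. The low figures need both a true SD near 36% and near-zero values. In the bounded model at margin 1.34 with floor 1/60, power is 91% if the SD is 22% and 97% if it is 20%.

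The design also makes 8% zero adherence among evaluable participants a strong assumption. Section 8.6 has intervention participants checked every 15 days and reassigned to daily observation after more than five missed tablets in a refill period, and has control participants observed each business day. The 10% attrition allowance may already absorb early defaulters. The protocol does not say whether it does. All of this stands, and it limits the claim about power.

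It is also true that reproducing 57 does not by itself identify the scale. The formula depends only on 36/20 = 1.8, so a log10 SD of 0.36 with a log10 margin of 0.20 (ratio 10^0.20 = 1.58) would give the same number. The wording rules this out, since both figures are attached to percentage adherence with a mean of 79%.

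Finally, the handling of zeros is commonly left to a statistical analysis plan, so its absence here is not counted as an error. None of these points removes the mismatch. The protocol itself fixes the margin, the sample size, the transform and the form of the comparison, and they do not fit together.

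**Conclusion.** The point holds as a contradiction of scale within the protocol. The sample size and margin belong to a raw difference of 20 percentage points, and the planned non-inferiority comparison is a ratio of geometric means with no stated margin. As written, the primary adherence decision has no usable criterion, and the 80% power does not apply to the planned test.

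The true power of that test cannot be determined from the protocol. At SD 36% and 51 evaluable per arm it ranges from about 10% to 92%, depending on an assumed distribution, an assumed treatment of near-zero values and an assumed ratio margin. A shortfall is the more likely direction, because the protocol's own mean and SD fit a log-normal badly and the log magnifies the lower tail. That is a judgement about direction and does not establish a size. The mismatch needs correction before analysis because it concerns the primary conclusion.

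**What to change.** In sections 8.5.1.5 and 9, make the primary adherence analysis the difference in mean percentage adherence, intervention minus control, with a two-sided 95% confidence interval (Welch or bootstrap). Declare non-inferiority if the lower limit is above -20 percentage points, and keep zero adherence as zero. Report the geometric mean ratio as a sensitivity analysis.

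This costs wording only, with no extra participants or data. It brings the test back to the scale on which 57 per arm was computed, with about 80% power under the protocol's own inputs.

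If the ratio is kept as primary, the contradiction can also be resolved by stating the ratio margin, a log-scale SD with its basis and a rule for zeros, and restating the power for 57 per arm. That route may show that more participants are needed. Under the log-normal assumption, margins of 1.25 and 1.20 call for 67 and 100 per arm after attrition.

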### **8.5.2. Provider participants**

#### **8.5.2.1. Study population**

Here, the source population will be healthcare providers who give TB treatment in public health care facilities. The study population is all adults in the study sites who are currently providing TB treatment under DOT.

#### **8.5.2.2. Inclusion criteria**

Inclusion criteria will include:

- A healthcare provider with academic qualification as a medical doctor, health officer (BSc), or nurse (BSc or Diploma);
- At least three months of experience providing DOT services in the facility;
- Able and willing to provide informed consent

#### **8.5.2.3. Exclusion criteria**

The exclusion criteria are:

- Not trained or is not familiar with DOT,
- Expected to move away from the facility before completion of enrolment of study patients

#### **8.5.2.4. Justification for inclusion and exclusion**

Health care providers who are not trained on DOT or do not have experience of the service would not be able to share their experience on DOT and handle patients per the need. A healthcare provider who is already known to leave the facility before completion of the study would interrupt the data collection process and affect the quality and outcome of the study.

#### **8.5.2.5. Sampling and sample size**

The study intends to involve 10 health facilities. Thus, a total of 10 healthcare providers, one from each, who are providing DOT in the data collection period will be identified purposively and enrolled. A list of reserves, one from each facility, will be kept to engage in case of any provider missing.

### **8.6. Interventions**

Participants in the intervention arm will receive a 15-days TB medication supply (HRZE fixed-dose combination therapy of 15 doses) in an electronic pillbox device (evriMed500 digital medication monitoring and reminder device manufactured by Wisepill Technologies, South Africa) to self-administer. Providers will collect baseline data, including demographic, socioeconomic, behavioral, and social factors using the study's baseline questionnaire. Based on the baseline data, participants will be clustered into four behavioral determinants (use cigarettes, alcohol, Khat - a psychostimulant plant, and cocaine/marijuana) and three social determinants (homeless, unemployed, and illiterate) as appropriate for the purpose of analysis. Participants in this arm will return every 15 days, where the provider will count any remaining tablets in the pillbox, download the pill-taking data from the Wisepill device, evaluate the functionality of the device and troubleshoot as needed, and perform the urine

isoniazid test. The level of adherence in their intensive phase of treatment will be calculated using the medication possession ratio (MPR). Any participant who misses more than five tablets in any 15- day refills will be reassigned to daily DOT throughout the remaining days of the intensive phase. Participants in the intervention arm can consult the healthcare provider in cases of medical illness or any adverse events outside of a scheduled visit before the next appointment. The phone number of the healthcare provider following their TB condition will be written at the backside of their appointment cards. The phone call strategy aims to maintain the DOT advantage for the intervention arm.

Participants in the control arm will get their treatment as per the standard practice of DOT, where participants will visit the healthcare facility each business day throughout the two months intensive phase to swallow their daily dose of HRZE with direct observation by the healthcare provider. Additionally, they will be given pills for the weekend to take them at home. The provider will collect baseline data, conduct a urine isoniazid test every 15-days, and cluster participants into behavioral and social determinants as applicable for participants in the intervention arm. For this arm, the management of participants who interrupt treatment will follow the national TB treatment guidelines.

Both arms will be followed up throughout the intensive phase which lasts for two months. The continuation phase (4 months) will follow the standard DOT practice for both arms. Both arms will have a TB care and treatment service free of charge, and the pillbox will be given to each participant in the intervention arm free of charge. For both arms, participants will receive treatment according to Ethiopian national TB treatment guidelines.

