# 1. PROTOCOL SUMMARY

## 1.1. Synopsis

Title: Electronic pillbox-enabled self-administered therapy versus standard directly observed therapy for tuberculosis medication adherence and treatment outcomes in Ethiopia: a multicenter randomized controlled trial (SELFTB trial)

Hypothesis: The use of a digital medication event reminder and monitor device-observed self-administered therapy provides non-inferior medication adherence and treatment outcomes for patients with TB compared with the standard in-person directly-observed therapy (DOT) in Ethiopia, one of the low-income countries with the highest burden of TB.

Objectives: Primary objectives:

1. To assess whether a digital medication event reminder monitor (MERM) device-observed self-administered therapy improves adherence in patients with TB compared with the standard DOT.
2. To assess whether MERM-observed self-administered therapy improves treatment outcomes in patients with TB compared with the standard DOT.

Secondary objectives:

3. To evaluate if MERM-observed therapy provides higher health-related quality-of-life (HRQoL) and lower catastrophic costs compared to the standard DOT
4. To evaluate the patient-reported usability and treatment satisfaction with MERM-observed self-administered TB therapy compared with the standard in-person DOT.

Outcome measures: Primary outcomes:

1. Level of adherence: Individual-level percentage adherence over the two-month intensive phase measured by adherence records compiled from MERM device vs. DOT records.
2. Sputum conversion: Participants with sputum smear converted following the standard two-month intensive phase treatment.

Secondary outcomes

3. Negative IsoScreen urine isoniazid test: Participants having at least one negative urine isoniazid test result (IsoScreen test, GFC Diagnostics Ltd, Bicester, England)

4. Adverse treatment outcome: Participants having at least one of the three events: treatment not completed; death; or loss to follow-up
5. Self-reported adherence: Participants who self-reported to have forgotten to take their medication
6. Health-related quality of life (HRQoL): The association between MERM-observed therapy and HRQoL, with the HRQoL measured and calculated for each participant by arm using the EuroQoL 5-dimension 5-level (EQ-5D-5L) score ranging from 0 to 1, with a higher score designating better HRQoL.
7. Catastrophic costs: Participants with overall TB treatment cost exceeding or equivalent to 20% of their income.

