The device has a medication intake event in an electronic record that is created when a patient opens the device to take his or her medication. It consists of a date-and-time stamp. The dispenser provides an electronic heartbeat to a central management system whenever medication is taken, and this also indicates that the device was functioning during that period.

The alarm period is 30 minutes in length and consists of three-alarm cycles. The alarm cycles are 10 minutes each and made up of two parts. These alarms apply regardless of the type of reminder selected. The first five minutes of the alarm cycle is the active alarm. During the active alarm, the buzzer will sound, and the green LED will flash in the following sequence: short, short, long. The yellow LED will flash if the “Refill Alarm” is configured and the date is less than or equal to the current date. The second five minutes of the alarm cycle is the passive alarm. During the passive alarm, the buzzer will not sound, and the green LED will not flash. The yellow LED will continue to flash if the “Refill Alarm” is configured and the date less than or equal to today. Opening the container will cancel the active alarm if it is opened within four hours before the scheduled alarm or if it is opened during the alarm period.

The evriMED500 makes use of two AA batteries which should last for more than 12 months. Regarding storage capacity, it can store more than 12000 records/events. The evriMED PC Application is configured by the evriMED PC Application and it allows a direct connection to the evriMED device via a USB cable. Specification of the evriMED500 is summarized in table 2.

**Table 2:** Summary of evriMED500 specification

| Item                                                     | Specification                                                           |
|----------------------------------------------------------|-------------------------------------------------------------------------|
| Data Storage                                             | 12000 records                                                           |
| Battery Life (Alkaline)                                  | 12+ months                                                              |
| Power requirements                                       | Two AA batteries                                                        |

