For both arms, the providers will collect baseline data, including demographic, socioeconomic, behavioral, and social determinants social using the study's baseline questionnaire. For participants in the intervention arm, the providers will orient participants in the intervention arm as they enroll about how to use the evriMED500 device. The orientation time will depend on the efficiency of the participants to fully acquire and demonstrate the necessary skills. Providers will then dispense a 15-days TB medication supply (HRZE fixed-dose combination therapy of 15 doses) to participants within the evriMed500 device for self-administration. Providers will collect sputum specimens from participants; write their cell phone numbers at the backside of participants' appointment cards to communicate in cases of medical illness or any adverse events before the next appointment, and inform them to return every 15 days. When participants returned, the providers will count any remaining tablets in the pillbox, download the pill-taking data from the evriMED device, check functionality of the device, and conduct a urine isoniazid test. The providers will fill out the study's adherence follow-up form to capture information if the drugs are taken every day, and if not, the reasons for non-adherence. The providers will then evaluate the level of adherence based on the preset criteria, and refill a 15-day TB medication supply in the same pillbox as appropriate. The providers will collect sputum specimens from participants at the end of the intensive phase.

For the control arm, providers will handle participants according to the standard DOT procedure, where participants will visit the healthcare facility each business day in the intensive phase to swallow their daily dose of HRZE with direct observation by the provider. The providers will fill out a similar adherence follow-up form for the control arm. Additionally, if a participant in the control arm requests medications

for self-administration, the provider will collect information about the date requested and for how many days requested on the follow-up form.

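### Section 8.6 scores intervention-arm adherence with an undefined medication possession ratio that conflicts with the device-record primary outcome and, if read as supply, hides missed doses

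*Protocol*

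**What the plan says.** The protocol describes intervention-arm adherence in several places, and they do not agree.

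- **Primary outcome (Synopsis, repeated in section 6.1.1):** "Individual-level percentage adherence over the two-month intensive phase measured by adherence records compiled from MERM device vs. DOT records". This names a data source for each arm but gives no formula.
- **Interventions (section 8.6):** "The level of adherence in their intensive phase of treatment will be calculated using the medication possession ratio (MPR". The sentence stands in the paragraph on the pillbox arm. No such ratio is mentioned for control.
- **Analysis (section 9):** t-tests on log-"transformed adherence percentage of the expected 60 days". This supplies a denominator but no numerator.
- **Supply (section 8.6):** "Participants in the intervention arm will receive a 15-days TB medication supply (HRZE fixed-dose combination therapy of 15 doses". Section 8.7 has providers assess adherence at each return and then "refill a 15-day TB medication supply in the same pillbox as appropriate".
- **Data taken at each return (section 8.6):** "the provider will count any remaining tablets in the pillbox, download the pill-taking data from the Wisepill device".
- **What the device logs (section 8.1):** "The device has a medication intake event in an electronic record that is created when a patient opens the device", with date and time.

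Section 8.8 defines eleven terms. The possession ratio is not among them. Section 8.8.1 defines medication adherence by what patients take, not by what they hold.

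**The concern.** A possession ratio, in its usual sense, is days of supply held divided by days in the period. It measures dispensing. When 15 doses are handed out for 15 days, a patient who returns on time has full possession however often the box was opened. The control arm would be scored from daily DOT records, so missed doses would count there and not in the pillbox arm.

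In a non-inferiority trial, a measure that overlooks missed doses in the experimental arm alone favours the claim under test. Section 8.6 is also the only place that names a calculation for the intervention-arm level, so an analyst following it literally could use this ratio for the first primary outcome.

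**Working it through.** **1. The plan's own sample size, to fix the inputs.** Section 8.5.1.5 gives one-sided alpha 2.5%, power 80%, SD 36%, margin 20% (read as percentage points), mean adherence 79% in both arms and 10% attrition.

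n per arm = 2 × (1.96 + 0.84)² × 36² / 20² ≈ 50.9, so 51 evaluable. Then 51 / 0.90 = 56.7, so 57. The stated 57 per arm reproduces.

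**2. Supply-based ratio for a regular attender.** Four supplies × 15 doses = 60, and 60 / 60 expected days = 100%. The number of doses taken does not enter.

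**3. What that can hide.** Section 8.6 moves a participant to daily DOT after more than five missed tablets in a refill period, so five missed tablets per period stays below the trigger. Tablets per dose is not stated, so it is an assumption:

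| Tablets per dose (assumed) | Whole doses missed per period below the trigger | True intake over 60 days | Supply-based score |
|---|---|---|---|
| 1 | 5 | 40/60 = 67% | 100% |
| 2 | 2 | 52/60 = 87% | 100% |
| 3 to 5 | 1 | 56/60 = 93% | 100% |

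A period in which the trigger is exceeded would itself score 15/15. How the days after the move to daily DOT are scored is not stated.

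**4. What lowers the ratio.**
- Stopping after 1, 2 or 3 supplies: 15/60 = 25%, 30/60 = 50%, 45/60 = 75%.
- Each of three refills late by 1, 3 or 5 days, with the period extended to match: 60/63 = 95%, 60/69 = 87%, 60/75 = 80%.

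**5. Effect on the conclusion.** Simulation of 20,000 trials with 51 evaluable per arm. Control is normal with mean 79 and SD 36. Non-inferiority is declared when the lower 95% limit for intervention minus control exceeds −20 points.

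Supply-based ratio, with an assumed share stopping early (equally likely after 1, 2 or 3 supplies) and everyone else at 100%:

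| Share stopping early | Mean ratio | Non-inferiority declared |
|---|---|---|
| 0% | 100% | 1.00 |
| 10% | 95% | >0.99 |
| 20% | 90% | >0.99 |
| 30% | 85% | 0.98 |
| 50% | 75% | 0.69 |

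Dose-taking records, SD 36 in both arms:

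| True intervention mean | Non-inferiority declared |
|---|---|
| 79% | 0.79 |
| 69% | 0.28 |
| 59% (at the margin) | 0.025 |

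The first table does not depend on how many doses continuing attenders miss; the second does.

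**The case against.** The strongest reply is that the protocol does not make a supply-based ratio its primary outcome. The Synopsis, section 6.1.1 and the tools listed in section 8.7 all point to device records against DOT records, and section 9 uses 60 expected days. One sentence in the Interventions section differs. It comes straight after the tablet count and the download and just before the missed-tablet rule, so doses taken over doses prescribed may have been meant. On that reading the automatic 100% disappears. The exact formula may also be in a SAP that is not at hand.

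Most of this stands, and it limits the point. A reader might infer more than the text supports:

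- *That the pillbox arm cannot look inferior.* Late returns, early stopping and withheld refills all reduce the ratio.
- *That someone taking nothing would score 100% over two months.* The missed-tablet rule and the adherence check before each refill mean such a person should not receive four supplies.
- *That the device data are discarded, or that there are three competing primary numerators.* Tablet counts and downloads are visit procedures. Only device records are named in the outcome definition.
- *That control is scored purely on witnessed intake.* Weekend doses go home (about 2 in 7, assuming a five-day working week), and section 8.7 allows for further approved self-administration.
- *That a built-in gain of 100 − 79 = 21 points matters because it exceeds the 20-point margin.* The margin is a tolerance for being worse, so the two are not comparable.

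The reply does not remove the contradiction. A SAP formula would still conflict with the protocol's sentence, and under either reading the term is wrong or undefined.

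**Conclusion.** The point holds as an internal contradiction about how a primary outcome is computed: an undefined possession ratio in section 8.6 against device records in the Synopsis and section 6.1.1, with a 60-day denominator in section 9. Whether it biases the result depends on the reading. If the ratio means supply, it is at or near 100% for on-time attenders and hides missed doses in the intervention arm only. If it means doses taken, the defect is a misleading label with no formula.

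On the supply reading, the hidden shortfall below the missed-tablet trigger runs from 33 points (100 − 67, one tablet per dose) to about 7 points (100 − 93, three to five tablets per dose). The larger figure could change the conclusion. The smaller one would not do so against the planning mean of 79%.

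The simulated probabilities are illustrative. The shares stopping early are assumed, and the raw percentage scale of the sample size calculation is used, whereas sections 8.5.1.5 and 9 plan a log-transformed analysis. The simulation shows the direction and possible strength of the bias. It does not show that non-inferiority is guaranteed.

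**What to change.** Delete the possession-ratio sentence in section 8.6 and put one rule in sections 6.1.1, 8.6 and 9:

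- **Adherence:** days with a recorded dose divided by the 60 expected days, in both arms.
- **Recorded dose, intervention:** a device opening on that day while the participant is on the pillbox, and a DOT-record entry after any move to daily DOT.
- **Recorded dose, control:** a DOT-record entry, with a stated rule for how weekend and other home doses are counted.
- **Cross-check:** report the tablet count beside the device record, and list the participants in whom the two differ.

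If the authors meant doses taken over doses prescribed, drop the term and write that formula instead.

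The cost is a short text amendment, matched in the SAP if there is one. Device downloads, tablet counts and DOT records are already planned. Nothing in treatment or follow-up changes.
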